**Fig. 2 Fig2:**
[figure not shown]
SPIRIT figure – summary of study procedures for intervention and control arms

Participants in both the intervention and control arms will be given a MERM box and 30 days of medication, which they will be asked to keep in the MERM. The box records the date and time of each opening. Participants will return to the TB dispensary/hospital for each of six monthly follow-up visits (months 1–6). Patients in the intervention arm will be required to bring their MERM to each monthly follow-up visit, at which the doctor or designee will connect it to the computer and download the data. In the control arm, the MERM is in silent mode (no audio or visual reminders) and data from the box will be downloaded once, at the end of treatment or earlier if the patient stops using the MERM before the end of treatment; the doctor will not be able to access these adherence data. In either arm, if applicable, the doctor or designee will assist the patient to fix any problems with the box and, if necessary, to replace it.

Sputum will be collected at the end of the second month for an exploratory endpoint of 2-month smear conversion and again at the end of treatment for culture (using Lowenstein–Jensen) and smear to enhance the definitions of treatment ‘cure’ and ‘failure’.

Following the end of treatment, the treatment outcome, as recorded by the National TB Control programme, will be abstracted. Patients will be seen at the TB hospital/dispensary at two further follow-up visits, at 12 and 18 months after start of treatment, for a chest x-ray and to collect a sputum specimen for culture in order to measure recurrence. Patients will also be asked about TB symptoms and whether they have re-started TB treatment. The hospital/dispensary doctor, nurse or other staff member will help facilitate patient attendance at these post-treatment follow-up visits. In addition, these patients will be telephoned at months 9 and 15 after the start of treatment and asked about TB symptoms and whether they have re-started TB treatment. Patients with TB symptoms will be advised to attend a healthcare clinic. If a patient has restarted TB treatment, information from the TB register and TB diagnosis will be abstracted.

Participants are free to withdraw from the study at any time and those in the intervention arm can stop using the MERM, whilst remain in the study, at any time. Participants will also be withdrawn from the study if they plan to move away or travel continuously for more than 1 month, or if they are no longer using daily fixed-dose combination tablets. All participants who withdraw early will be asked if we can still collect their treatment outcomes and contact them for post-treatment follow-up. No other changes to care are prohibited during the trial.

A pilot study enrolled 55 patients in four counties/districts before commencing enrolment into the trial to field test the MERM and associated software, the recruitment process, the monthly adherence feedback given to patients by the managing Doctor and case report forms. Following the pilot study, all 24 counties/districts had a 3-month run-in period to help staff familiarise themselves with the recruitment and follow-up processes and ensure all monitoring processes are being implemented.

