### Trial outcomes

The primary outcome is a composite poor outcome measured over 18 months from start of TB treatment, defined as either of poor outcome at the end of treatment (death, treatment failure or loss to follow-up) or subsequent recurrence (culture positive for TB at 12 or 18 months or re-starting TB treatment in the follow-up period). Secondary outcomes are three clinical outcomes and two adherence outcomes: poor outcome at the end of treatment; composite poor outcome measured at 12 months; lost to follow-up during treatment; percentage of months in which the patient missed at least 20% of doses, measured using data from the MERM; and percentage of total doses missed. Cost-effectiveness outcomes include mean cost per patient treatment month for each arm, and incremental cost of the intervention per patient completing treatment, per death and per disability-adjusted life year averted.

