### Statistical analysis

Analyses will use an intention-to-treat approach with methods appropriate for the clustered randomised trial design, giving each cluster equal weight [10]. Quantitative outcomes will be summarised as the mean for each cluster and the difference of means for intervention versus standard of care arm. For binary outcomes or rate outcomes, the overall risk (rate) for each cluster will be calculated as well as the ratio for intervention versus standard of care arm. An adjusted analysis will be conducted to control for baseline imbalance of patient or district/county level factors across control and intervention arms. Subgroup analyses will be conducted for the primary outcome and may include urban/rural, gender, literacy levels, migrant/non-migrant and type of healthcare provider. A statistical analysis plan will be finalised prior to the end of data collection.

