## Preliminary data from the run-in period

A 3-month run-in period was conducted in all 24 clusters. TB patients recruited during this period will be followed up at the end of treatment but not contribute to the trial outcomes. Overall, 485 patients have been recruited, of which 73% are male, median age 40 years (interquartile range: 27–57 years), 7% are illiterate and 64% had smear-positive TB (Table 2). Most characteristics were similar to those observed in the first study, but patients in this study were less likely to be living in their place of registration (69% vs. 91%) and were more likely to have smear-positive TB (64% vs. 36%).

**Table 2 Tab2:** Data from run-in period from the 24 clusters (*n* = 485)

Characteristic	Category	Number	Percent
Gender	Female	132	27.2%
Age, years	18–29	152	31.3%
	30–39	87	17.9%
	40–59	149	30.7%
	60+	97	20.0%
Farmer	Yes	226	46.6%
Education, highest level	Illiterate	36	7.4%
	Primary School	134	27.6%
	Junior Middle School	178	36.7%
	High School (Technical School)	81	16.7%
	University or more	56	11.6%
Marital status	Single	119	24.5%
	First marriage	337	69.5%
	Other	29	6.0%
Residency	Place of registration	336	69.3%
Monthly household expenditure, CNY	< 1000	58	12.0%
	1000–3000	255	52.6%
	3001–5000	132	27.2%
	> 5000	40	8.3%
Distance to TB clinic, km	0–9	170	35.1%
	10–29	203	41.9%
	30–39	45	9.3%
	40+	67	13.8%
Distance to local village/township doctor, km	0–1.9	247	50.9%
	2–2.9	109	22.5%
	3+	129	26.6%
Smear status	Positive	309	64.1%

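### Compulsory withdrawal for moving, long travel or leaving fixed-dose tablets makes later outcome data depend on renewed agreement and so puts intention-to-treat ascertainment at risk

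*Protocol article*

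**What the plan says.** The Study procedures section of the protocol article gives two compulsory grounds for withdrawal after enrolment. The first is "Participants will also be withdrawn from the study if they plan to move away or travel continuously for more than 1 month"; the second follows directly: "or if they are no longer using daily fixed-dose combination tablets". No time limit within the 18 months is attached to the first. The second can only operate during treatment.

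The next sentence deals with data after withdrawal: "All participants who withdraw early will be asked if we can still collect their treatment outcomes and contact them for post-treatment follow-up". The same paragraph lets intervention-arm participants stop using the medication monitor while staying in the study.

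The Trial outcomes section sets the primary outcome over 18 months, "defined as either of poor outcome at the end of treatment (death, treatment failure or loss to follow-up) or subsequent recurrence". The Statistical analysis section states: "Analyses will use an intention-to-treat approach with methods appropriate for the clustered randomised trial design, giving each cluster equal weight". No sentence in the article excludes withdrawn participants from the analysis.

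**The concern.** A planned move or a long absence is a plausible route to loss to follow-up. Leaving fixed-dose tablets may accompany toxicity or failing treatment, although the article gives no reasons or frequencies. The triggers may therefore predict the endpoint. They are applied by the trial, after clusters have been allocated, to people who have not asked to leave.

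Once someone is withdrawn, end-of-treatment and 12- and 18-month information depends on a fresh yes. Those who say no, or who cannot be reached to be asked, have no outcome. The trial is unblinded, and intervention-arm doctors set aside travel periods when they review monitor data each month (Table 1). Control-arm doctors have no such task. The frequency of withdrawal could therefore differ by arm. If it did, and if those withdrawn were at higher or lower risk than the rest, the primary risk ratio would be biased. A later analysis plan can say how withdrawn people are scored, but it cannot supply cultures that were never taken.

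**Working it through.** **1. The plan's own figure.** Inputs from Sample size considerations: 12 clusters per arm (c), 125 patients per cluster, 5% unascertained, so m = 125 × 0.95 = 118.75; control risk p0 = 0.18; 40% reduction, so p1 = 0.108; coefficient of variation k = 0.25. Alpha is not stated; two-sided 5% is assumed.

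Power = Φ( √[(c − 1)(p0 − p1)² / V] − 1.96 ), with V = p0(1 − p0)/m + p1(1 − p1)/m + k²(p0² + p1²).

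- V = 0.1476/118.75 + 0.096336/118.75 + 0.0625 × 0.044064 = 0.001243 + 0.000811 + 0.002754 = 0.004808
- (c − 1)(p0 − p1)² = 11 × 0.005184 = 0.057024
- √(0.057024/0.004808) = 3.444, and Φ(1.484) = 93.1%

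A noncentral t version with 22 degrees of freedom gives 93.0%. The stated 92% is reproduced to within about one point.

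**2. Effect on power.** With the risks unchanged and more outcomes missing:

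| Unascertained | Power |
|---|---|
| 5% | 93.1% |
| 10% | 92.6% |
| 15% | 91.9% |
| 20% | 91.2% |
| 25% | 90.4% |

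Exceeding the 5% allowance costs little, because between-cluster variation is the largest term in V.

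**3. Effect on the risk ratio.** Suppose there is no true effect and the risk is 18% in both arms. Let w be the share withdrawn without an outcome and h the share of those who would have been events. The risk among the rest is (0.18 − w × h)/(1 − w). The article gives neither w nor h, so all values below are assumptions.

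5% withdrawn in the intervention arm, 1% in the control arm, none recovered:

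- h = 0.5: 0.155/0.95 = 0.163 against 0.175/0.99 = 0.177; ratio 0.92
- h = 0.8: 0.140/0.95 = 0.147 against 0.172/0.99 = 0.174; ratio 0.85
- arms reversed: 1.08 and 1.18

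Other assumed shares:

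- 5% in each arm, same h: 1.00
- 10% intervention, 5% control: 0.89 (h = 0.5), 0.75 (h = 0.8), 1.00 (h = 0.18, withdrawal unrelated to outcome)
- 5% intervention, 10% control: 1.13 (h = 0.5), 1.33 (h = 0.8)

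**4. If half the outcomes are recovered.** Assume that recovery is unrelated to outcome, so that 5% and 1% become 2.5% and 0.5%.

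- h = 0.5: 0.1675/0.975 = 0.172 against 0.1775/0.995 = 0.178; ratio 0.96
- h = 0.8: 0.160/0.975 = 0.164 against 0.176/0.995 = 0.177; ratio 0.93

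**5. Reading.** With no true effect, the ratio leaves 1.00 only when withdrawal without an outcome is both related to outcome and different between arms. The shift can go either way, and it shrinks as outcomes are recovered.

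**The case against.** A reader might infer that the rule takes likely events out of the primary analysis and contradicts intention-to-treat. The documents do not support that. Intention-to-treat is stated, no sentence drops withdrawn participants, and everyone who withdraws is asked to allow outcome collection and later contact. The Study procedures section also abstracts the treatment outcome recorded by the national programme.

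Three further inferences fail:

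- **The unblinded doctor chooses between loss to follow-up and withdrawal.** The article does not say so. Control patients are also seen monthly, non-attenders are traced in the same way in both arms (Table 1), and the withdrawal triggers are not read from monitor data.
- **The rule will be used often because 31% of run-in patients lived away from their place of registration** (69% lived there, against 91% in the first study). Living elsewhere is not planning to leave, and eligibility already requires likely residence for 18 months.
- **The bias favours the intervention.** Nothing supports that direction. The Background reports lower loss to follow-up in all three intervention arms of the previous trial.

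The analysis plan, which is not shown, may settle how departures are scored, and the consent form, also not shown, may already cover follow-up after withdrawal. These objections stand. They limit the point to data collection: nothing in the article keeps these participants in follow-up by default, and an analysis plan cannot recover missing 12- and 18-month cultures.

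**Conclusion.** The point holds as a risk to ascertainment. The protocol withdraws participants after allocation for reasons plausibly linked to the primary outcome and leaves their outcomes dependent on renewed agreement. Under the assumed 5% against 1% with no recovery, the distortion of a null risk ratio is 0.92 to 0.85, or 1.08 to 1.18 if reversed. It is smaller with partial recovery and absent if withdrawal is balanced in share and risk. These figures show what could happen; they do not estimate what will, because the article gives no withdrawal rates, no event risk among the withdrawn and no rate of agreement. The sample size is not in question. This is a cheap improvement to a stated data-collection rule and does not show the planned analysis to be invalid.

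**What to change.** Reword the withdrawal sentence to separate stopping study procedures from leaving the study, as the protocol already does for intervention-arm participants who stop using the monitor:

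- Participants who plan to move, travel for more than 1 month or are no longer on fixed-dose tablets may stop the monitor and study procedures. By default they remain in follow-up and in the intention-to-treat set, within the consent given.
- Their programme-recorded treatment outcome is abstracted, and the contacts at months 9, 12, 15 and 18 are attempted.
- Only the participant's own withdrawal of consent ends data collection.
- Departures during treatment are classified by one rule, applied identically in both arms.
- Departures are reported by reason and arm.

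This concerns data collection and outcome classification only, not clinical care. The cost is a protocol sentence, a site memo, some extra tracing, and accepting that some follow-up will be by telephone only, without culture. Register abstraction and telephone contacts are already in the plan. The consent form should be checked first to confirm that it covers continued follow-up.

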### Data management

The treating doctors will be trained and responsible for collecting written, informed consent, assessing eligibility, and capturing all data into a bespoke database. A password will be required to gain access to the database. Data will be validated on entry, using range and consistency checks. Logical data checks will also be performed on the data. Incomplete and incorrect data queries will be sent back to sites electronically for error resolution. All study records will be managed in a secure and confidential fashion. All records will be stored at the participating TB clinics and offices at provincial level in locked filing cabinets and access to the records will be restricted to specified study team members. Case report forms will be identified using the participant’s study number only, with locator information stored separately. When datasets are generated for data analysis, personal identifiers will be removed. All records will be archived in a secure storage facility for at least 10 years after the completion of the study.

### Statistical analysis

Analyses will use an intention-to-treat approach with methods appropriate for the clustered randomised trial design, giving each cluster equal weight [10]. Quantitative outcomes will be summarised as the mean for each cluster and the difference of means for intervention versus standard of care arm. For binary outcomes or rate outcomes, the overall risk (rate) for each cluster will be calculated as well as the ratio for intervention versus standard of care arm. An adjusted analysis will be conducted to control for baseline imbalance of patient or district/county level factors across control and intervention arms. Subgroup analyses will be conducted for the primary outcome and may include urban/rural, gender, literacy levels, migrant/non-migrant and type of healthcare provider. A statistical analysis plan will be finalised prior to the end of data collection.

### Ethics and dissemination

The trial has approval from the Institutional Review Board of the Chinese Center for Disease Control and Prevention (ref: 201603) and the London School of Hygiene & Tropical Medicine Ethics Committee (ref: 10665). It is registered with Current Controlled Trials (identifier ISRCTN35812455). Participants in both intervention and control arms will receive around 200 RMB (in total; approximately US$30) if they attend for study review visits at 12 and 18 months after enrolment, as compensation for their time and travel expenses. In addition, all patients will benefit from a free GeneXpert test at enrolment, allowing quick diagnosis of drug resistance to rifampicin, as well as free cultures at the end of treatment and at 12 and 18 months. Written, informed consent will be sought from potential participants by their treating doctor (as trained by the study team), using standard consent forms and information sheets available in Chinese Mandarin.

The trial results will be communicated to stakeholders through dissemination meetings. Investigators will present results at relevant conferences and submit manuscript(s) to peer-reviewed journals. Public access to the participant-level dataset of main trial results and statistical code will be made available.

### Trial governance

[name] is the Chief Investigator and is employed by the Chinese Center for Disease Control and Prevention, which is the trial sponsor. The trial sponsor had no role in the design of this study and will not have any role during its execution, analyses, interpretation of the data, or decision to submit results.

The trial investigator team is responsible for the trial design, leading the implementation, data analysis, publication, and determining authorship eligibility guidelines, while a trial implementation team is responsible for site training, study monitoring, auditing trial conduct in site visits once every 3 months, and day-to-day implementation of the trial. A trial steering committee oversees the trial, monitors its progress and provides advice to the Chief Investigator and trial investigator team.

The trial does not have a Data Monitoring Committee, as any potential harms to patients are thought to be low risk. The Patient Information Sheet contains two telephone numbers for the Principal investigator (author XL), in case the patient wants to ask anything, and this is the primary means by which patients can report problems with trial conduct. The Trial Steering Committee will review progress data and will thus partially function as a Data Monitoring Committee. Recruitment will take approximately 2 years, and for each individual in the study there will be a 6-month treatment period followed by a further 12 months of follow-up. At the time that recruitment ends, there will only be primary outcome data for approximately a quarter of participants. Hence, there is no planned interim analysis. Any major changes to the study would be updated in the protocol and trial registration, reported to the ethics committees for approval, and communicated to the trial steering committee at the next meeting.

## Preliminary data from the run-in period

A 3-month run-in period was conducted in all 24 clusters. TB patients recruited during this period will be followed up at the end of treatment but not contribute to the trial outcomes. Overall, 485 patients have been recruited, of which 73% are male, median age 40 years (interquartile range: 27–57 years), 7% are illiterate and 64% had smear-positive TB (Table 2). Most characteristics were similar to those observed in the first study, but patients in this study were less likely to be living in their place of registration (69% vs. 91%) and were more likely to have smear-positive TB (64% vs. 36%).

**Table 2 Tab2:** Data from run-in period from the 24 clusters (*n* = 485)

Characteristic	Category	Number	Percent
Gender	Female	132	27.2%
Age, years	18–29	152	31.3%
	30–39	87	17.9%
	40–59	149	30.7%
	60+	97	20.0%
Farmer	Yes	226	46.6%
Education, highest level	Illiterate	36	7.4%
	Primary School	134	27.6%
	Junior Middle School	178	36.7%
	High School (Technical School)	81	16.7%
	University or more	56	11.6%
Marital status	Single	119	24.5%
	First marriage	337	69.5%
	Other	29	6.0%
Residency	Place of registration	336	69.3%
Monthly household expenditure, CNY	< 1000	58	12.0%
	1000–3000	255	52.6%
	3001–5000	132	27.2%
	> 5000	40	8.3%
Distance to TB clinic, km	0–9	170	35.1%
	10–29	203	41.9%
	30–39	45	9.3%
	40+	67	13.8%
Distance to local village/township doctor, km	0–1.9	247	50.9%
	2–2.9	109	22.5%
	3+	129	26.6%
Smear status	Positive	309	64.1%

## Discussion

This large, pragmatic trial has been designed to determine whether a new patient management model, based around the MERM, results in improved clinical outcomes for TB patients. The aim of the trial is to inform government policy in China, and elsewhere, and is thus fundamentally a study of effectiveness rather than efficacy. For this reason, we have elected to conduct a highly pragmatic trial.

We have scored our trial using the PRagmatic Explanatory Continuum Indicator Summary (PRECIS-2) tool, which describes where a trial lies on the pragmatic/explanatory continuum across nine domains [15]. Two authors (JL and SS) scored the trial on each of the nine domains and discrepancies were resolved by a third author (KF). The trial scored as ‘very pragmatic’ on three domains, namely ‘recruitment’, ‘setting’ and ‘primary analysis’, and as ‘rather explanatory’ on three domains, namely ‘eligibility’, ‘flexibility – adherence’ and ‘follow-up’ (Fig. 3). The intervention is applicable for almost all TB patients using fixed-dose combination tablets, and so most of the eligibility criteria result from the needs of the trial. The primary outcome is measured over 18 months; therefore, we want to ensure that participants are planning on staying in the area for the next 18 months. To ensure comparability between participants, we also require them to be on treatment for the same duration, namely 6 months. We want to ensure that all participants have drug-sensitive TB to ensure the best chance of impacting a clinical outcome. The intervention is designed to maximise adherence to the intervention; thus, we have scored the ‘flexibility – adherence’ domain as ‘rather explanatory’, as suggested in the guidance [15]. All treating doctors are trained on the study procedures, but we do not enforce any aspect of the protocol, in line with the desire to make the trial as pragmatic as possible. There are three reasons why we scored ‘follow-up’ as ‘rather explanatory’; firstly, our primary outcome requires a follow-up visit at 6 and 12 months after the end of treatment; second, we will contact participants by telephone at 3 and 9 months after the end of treatment to see if they have restarted TB treatment; and finally, in some provinces, TB treatment now requires clinic visits less than monthly, which we require in the control arm. The average score across the nine domains was 3.6, with 1 being ‘very explanatory’ and 5 being ‘very pragmatic’.

